#### Economic evaluation

The marginal direct medical, non-medical and time cost differences will be calculated for the four treatment strategies. These will include the additional costs of laparoscopy, of fast track care, as well as the differences due to complications and readmissions.

### Data collection and monitoring

Data are collected via a secured Internet module which is specially designed for the LAFA-study. Data are collected daily until the day of discharge. Preoperatively, and at two and four weeks postoperatively the questionnaires (SF-36/GIQLI) are filled in by the patient. One month postoperatively, the general practitioner is contacted to inform whether he/she was contacted by the patient for problems related to the operation.

There will be regular contact between the study coordinators and the participating centers. One research fellow will monitor the included data of every patient.

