### Primary and secondary endpoint

The primary endpoint of the LAFA-study is total postoperative hospital stay in days, including hospital stay of patients who are readmitted within 30 days after surgery.

Secondary endpoints are quality of life at two and four weeks after surgery. Quality of life will be measured by two validated questionnaires; Short Form 36 (SF-36) and the Gastro-Intestinal Quality of Life Index (GIQLI). Further secondary endpoints are; medical and non medical costs, morbidity, and mortality within 30 days after surgery, patient satisfaction measured by standardized questionnaires, and readmission rate.

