#### Sample size calculation

Since both, fast track care and laparoscopy focus on earlier recovery resulting in a reduction of hospital stay, the latter is used as primary efficacy parameter. The mean postoperative hospital stay for segmental bowel resection with standard care is 9 days with a standard deviation of 2.5 days in the Academic Medical Center Amsterdam. Using a 5% significance level, a total sample size of 400 would have a power of >95% to detect a minimum reduction of 1 day in hospital stay between laparoscopic surgery and open surgery, a 1 day reduction in hospital stay between fast track care and standard care, and a power of 80% to detect the same difference between the combination of fast track care with laparoscopic surgery and current treatment.

A much larger difference can be expected between the treatment groups, for instance open surgery and standard care compared to fast track perioperative care and laparoscopic surgery. In order to obtain results with adequate precision we have calculated group size using a difference of 1 day rather than the expected 2–4 days. With a group size of one hundred patients per arm it is possible to find a significant difference (alfa = 0.05, beta = 0.1) of at least 10% in subscales of the SF-36, a validated Quality of life Questionnaire, at two weeks after surgery [22-24]. Liem *et al*. demonstrated 20–30% differences in subscales of the SF-36 between laparoscopic versus open hernia repair 1 week after surgery[24]. Maartense *et al*. found a 10% difference in physical and social function two weeks after surgery comparing laparoscopic versus open ileocolic resection in a randomized study from our institution[25].

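### Detection of 30-day complications that do not lead to readmission or death depends on length of stay, so arms with shorter stay may appear to have lower morbidity

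*Protocol article*

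**What the plan says.** The Protocol article, under Primary and secondary endpoint, lists among the secondary endpoints "medical and non medical costs, morbidity, and mortality within 30 days after surgery". The comma leaves slight doubt, but the 30-day window most naturally covers morbidity as well as mortality.

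Data collection and monitoring then gives the method:
- In hospital: "Data are collected daily until the day of discharge".
- After discharge, from the practitioner: "One month postoperatively, the general practitioner is contacted to inform whether he/she was contacted by the patient for problems related to the operation".
- After discharge, from the patient: "Preoperatively, and at two and four weeks postoperatively the questionnaires (SF-36/GIQLI) are filled in by the patient". The article describes both instruments as quality-of-life measures and does not say that they record complications.

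Two other endpoints bear on events after discharge. The primary endpoint is total postoperative stay, "including hospital stay of patients who are readmitted within 30 days after surgery", and the secondary endpoints include "patient satisfaction measured by standardized questionnaires, and readmission rate".

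On timing, Sample size calculation says: "The mean postoperative hospital stay for segmental bowel resection with standard care is 9 days with a standard deviation of 2.5 days". It plans for a 1-day reduction and expects 2 to 4 days between treatment groups, giving as its example open surgery with standard care against laparoscopy with fast track.

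**The concern.** The endpoint window is the same in every arm, but the observation method switches on the day of discharge. That day is the main component of the primary outcome, and both treatments are intended to shift it. A complication that begins on day 7 is recorded by the ward if the patient is still admitted. If the patient went home on day 5 and is not readmitted, the stated route to the record is that the patient contacted the general practitioner and the practitioner reports it a month after surgery.

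Randomization does not remove such a difference, because it arises after allocation and through the treatment effect itself. A larger sample does not remove it either. The direction is fixed: if detection is less complete after discharge than before, the error favours the arm with the shorter stay.

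The Background names postoperative morbidity among the outcomes on which the best combination is to be judged. The Economic evaluation brings cost differences due to complications into the comparison of the four strategies. Complications missed more often in the early-discharge arms could flatter both results.

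**Working it through.** **The plan's own figure.** The article gives no morbidity rate and no power for morbidity. Its only power figures are for stay (SD 2.5, difference 1 day, 5% level, taken as two-sided). Power = Φ(δ / (σ√(2/n)) − 1.96).
- Main effects, 200 v 200: 1 / (2.5 × √(2/200)) = 4.00, and Φ(2.04) = 97.9%, which agrees with the stated figure of more than 95%.
- Combination v current treatment, 100 v 100: 1 / (2.5 × √(2/100)) = 2.83, and Φ(0.87) = 80.7%, which agrees with the stated 80%.

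These figures reproduce, and nothing below changes them.

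**Days under daily observation.** With a 9-day stay, 9/30 = 30% of the window. At the planned 1-day reduction, 8/30 = 27%. At the expected 2- to 4-day reduction, 7/30 = 23% down to 5/30 = 17%.

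**Spurious difference.** Assumptions, none of them from the documents:
- True 30-day rate p = 30% in both arms (20% to 40% as a check).
- Onset time exponential with mean m = 4 to 10 days, truncated at 30: F(t) = (1 − e^(−t/m)) / (1 − e^(−30/m)).
- Every patient is discharged at the arm's mean stay L.
- Detection after discharge, relative to in hospital, s = 50% to 80%. This is an average over all later complications, including those that lead to readmission.

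Recorded rate = p × [F(L) + s × (1 − F(L))]. The difference between stays of 9 and L days is therefore p × w × (1 − s), where w = F(9) − F(L) is the share of complications that begin while only the longer-stay arm is still admitted.

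| Stay (days) | w at m = 4 / 7 / 10 | Difference, s = 0.8 | Difference, s = 0.5 |
|---|---|---|---|
| 9 v 8 | 3.0% / 4.3% / 4.5% | 0.2–0.3 points | 0.5–0.7 points |
| 9 v 7 | 6.8% / 9.3% / 9.5% | 0.4–0.6 points | 1.0–1.4 points |
| 9 v 5 | 18.1% / 21.6% / 21.0% | 1.1–1.3 points | 2.7–3.2 points |

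Ends of the range for a 2- to 4-day difference: 0.30 × 0.068 × 0.20 = 0.4 points, and 0.30 × 0.216 × 0.50 = 3.2 points (3.3 if the share is rounded to 22%). If s = 1, every entry is zero.

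Across true rates of 20% to 40%, the largest value at a 1-day difference is 0.40 × 0.045 × 0.50 = 0.9 points. The largest at 9 v 5 days is 0.40 × 0.216 × 0.50 = 4.3 points.

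**Effect on a test.** With 200 v 200 and 9 v 5 days, the chance of a falsely significant result in favour of the shorter stay (nominal 2.5%) is at most about 5.5% at s = 0.8, and about 7% to 15% at s = 0.5, over true rates of 20% to 40%. This is a severe setting, because the article's own example for the larger stay difference is a comparison of two single arms, not a main effect.

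**The case against.** The strongest objection is that a reader might infer that the practitioner contact is the only source after discharge and that early discharge could conceal serious harm. The documents do not support that. Days of readmission within 30 days count in the primary endpoint, and readmission rate and 30-day mortality are endpoints in their own right, so serious later events have a route to the record in every arm. What remains exposed is milder complications treated at home or in an outpatient clinic.

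A reader might also infer that shorter-stay arms will necessarily show lower morbidity. That goes too far: the bias vanishes if detection after discharge is complete, and no detection rate is given. The Discharge criteria section requires pain control on oral drugs, no nausea, solid food, bowel function and mobility. Many early complications would therefore delay discharge and be recorded on the ward. The calculation ignores this and so tends to overstate the effect. The criteria do not help with a complication that begins after the patient has gone home.

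A larger effect is also tempting. If 20% to 40% of complications arose in the days between the two discharge dates, the difference would be 0.30 × 0.20 × 0.20 = 1.2 points to 0.30 × 0.40 × 0.50 = 6 points. The onset model puts that share at about 7% to 22%, and the documents give no reason to assume more.

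Finally, the article condenses a fuller protocol that may specify a day-30 visit or a complication form. That is a fair reason to ask for confirmation first. It does not dispose of the point, which rests on a stated collection rule tied to discharge and not on silence.

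**Conclusion.** The point holds in limited form. As the article describes it, detection of 30-day complications that lead to neither readmission nor death depends on length of stay, and any shortfall in detection after discharge favours the arm with the shorter stay.

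The likely size is modest: about 0.4 to 3.2 percentage points for a 2- to 4-day difference at a 30% true rate, and under 1 point at the planned 1-day difference. Both figures rest on the assumed detection rate, onset distribution and true rate, and on discharge at the mean stay.

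Morbidity is a secondary endpoint for which the article gives no power, and the three research questions under Study objectives concern stay, quality of life and costs. The correction is still worth making, because the bias has a known direction, can carry into the cost comparison and is cheap to remove.

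**What to change.** Amend Data collection and monitoring so that complications are ascertained to day 30 in the same way and on the same postoperative days in all arms, whatever the discharge date:
- Add a short fixed list of complications to the two- and four-week questionnaires that patients already complete.
- Have the research fellow who already monitors every patient's data check the hospital record to day 30. This also covers the days after the four-week form.
- Keep the practitioner contact as a supplement.
- Report 30-day morbidity from these common sources, and show in-hospital morbidity separately.

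If the full protocol already provides this, a sentence saying so closes the point. The cost is one more questionnaire page and some record-checking time by existing staff. More minor complications will be recorded overall, so the rates will be higher than under the present scheme. No change to treatment, discharge criteria or sample size is needed.

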## Discussion

Fast track programs in colonic surgery have been introduced more than a decade ago with favorable early results. Many elements of these fast track programs are based on solid evidence derived from randomized trials and systematic reviews. However, it is quite surprising, that implementation in daily practice has so far stayed behind [26-28] This can partly be explained by the necessity to break with long-standing traditions, such as preoperative fasting, slow postoperative advancement of oral feeding, and delayed mobilization. In a recent systematic review including six comparative single centre studies, fast track programs were found to reduce the time spent in the hospital and were found to be safe in major abdominal surgery. However, this systematic review demonstrated that the evidence on fast track colonic surgery was scarce[29].

Both, laparoscopic surgery and fast track programs are costly and require extensive expertise. Laparoscopic surgery is costly due to expensive disposables and additional operating time. Furthermore, a considerable learning curve must be mastered. Only 5–8% of the colectomies are therefore done laparoscopically in the Netherlands. Fast track multimodal perioperative care requires additional personnel trained in several aspects of the fast track program to make the program work. It is clear that both, laparoscopic surgery and fast track programs enhance recovery and thereby reduce hospital stay[2,8,29-32]. Shortening hospital stay and reduction of morbidity are attractive, since both increase the availability of beds and might reduce the overall cost of hospital stay. However, despite the current enthusiasm and implementation into daily practice of fast track care and laparoscopic surgery, there are few data available that provide evidence on the optimal combination (laparoscopic or open surgery and fast track or standard care) in terms of shorter hospital stay, reduced morbidity and cost effectiveness.

The largest reduction in hospital stay can probably be achieved by a combination of fast track programs and laparoscopic surgery. However, it is not known what the additional costs of laparoscopic surgery or fast track programs are compared to the reduction in hospital stay that can be achieved with these programs. Since the average postoperative hospital stay after segmental colectomy is still considerable in the Netherlands as well as throughout Europe, an enormous improvement can be expected applying fast track programs and/or laparoscopy. What the relative contribution is in reduction in hospital stay of both methods is unknown. This must be assessed in a setting where patients are blinded for the approach of surgery. The randomized controlled LAFA-trial was conceived to determine whether laparoscopic surgery, fast track perioperative care or a combination of both is to be preferred over open surgery with standard care in patients undergoing segmental colectomy for malignant disease.

## Abbreviations

LAFA-trial: LAparoscopy and/or Fast track multimodal management versus standard care trial

ASA: American Society of Anaesthesiologists

ERAS^®^: Enhanced Recovery After Surgery

GIQLI: Gastro-Intestinal Quality of Life Index

SF-36: Short Form-36
